## Methods: patient and public involvement, trial design

### Patient and public involvement {11}

During the design phase of the trial, the plans were presented to the study sponsor’s service user advisory board, which led to an increase in the monetary reimbursement and less extensive questionnaire packages at follow-up measurement time points for participants. Likewise, progress will be reported yearly to the service user advisory boards of the participating institutions to enable client involvement regarding trial conduct. Furthermore, plain language summaries of findings are shared with the service user advisory boards, the Dutch Centre of Expertise on Personality Disorders (Kenniscentrum Persoonlijkheidsstoornissen), and relevant mental health service user organisations, as well as published on the trial website [54] and social media.

### Trial design {12}

The P-DAET study is a pragmatic, multicentre, randomised controlled, non-inferiority trial with two parallel groups with equal group sizes (planned total *N* = 358). PD patients are randomly assigned to either generalist (GIT-PD) or specialist treatment (MBT or ST) through variable block randomisation, stratified on the mental health institution level, with a 1:1 allocation.

## Methods: participants, interventions, and outcomes

### Trial setting {13}

This multicentre trial will recruit 358 participants across 11 outpatient sites affiliated with five major Dutch mental healthcare institutions, located in both urban and rural areas across four provinces in the Netherlands: Altrecht (Zeist; Nieuwegein; Houten), Arkin NPI (Amsterdam; Amersfoort), Dimence Groep (Almelo), GGZ Oost Brabant (Helmond; Oss; Boxmeer), and de Viersprong (West-Brabant; ‘s-Hertogenbosch). New study sites in these institutes may be added to improve inclusion rates, if they provide both generalist and specialist treatments in accordance with the criteria specified under Intervention description {15a}.

### Eligibility criteria for participants {14a}

Subjects are deemed eligible if they (a) meet the DSM-5 criteria for ‘severe’ or ‘extreme’ PD according to the AMPD, as assessed by the Semi-Structured Interview for Personality Functioning – DSM 5 (STiP-5.1). A ‘severe’ PD will be diagnosed if at least two of the four facets of the STiP-5.1 are scored as ‘severe’. This mimics the proposed DSM-5 diagnostic criteria for classifying any PD, in which moderate or greater impairments in at least two out of four facets must be manifested [46]. Additionally, participants (b) need to be at least 18 years old. Exclusion criteria are (a) a primary diagnosis of autism spectrum disorder or (b) any other mental disorder diagnosed that requires prior treatment, (c) an IQ lower than 75 and/or (d) legal incapacity, as appraised during intake at the participating sites.

### Eligibility criteria for intervention deliverers {14b}

Participating sites are eligible if they offer GIT-PD and offer at least one of the specialist treatments included in this trial (MBT or ST). Treatments and therapists at participating institutions must adhere to the specified criteria described under Intervention description {15a}.

### Intervention and comparator

#### Intervention description {15a}

The experimental and comparator interventions are 1) generalist treatment (GIT-PD) and 2) specialist treatment (ST and MBT) for severe PD, respectively. Both intervention types are distinguished based upon a) level of speciality, b) format and content of the program, c) team discipline mix, d) required level of training and supervision, and e) dosage and duration of treatment.

##### Generalist condition (GIT-PD)

 Level of Speciality: GIT-PD is a non-theoretical and non-methodological approach without a specific theory of aetiology for PD. Rather, GIT-PD builds upon treatment as usual and improves regular care by implementing a framework of common factors derived from evidence-based treatments for PD [31]. These common factors include basic skills to build a relationship (empathy, positive regard, authenticity), to address ruptures, to reach consensus on goals and tasks, and to increase (affective) self-reflection and expression of emotions, inviting the application of a wide array of therapeutic techniques with varying aetiological backgrounds (e.g. behavioural, cognitive, psychodynamic) directed at goals of the individual patient. GIT-PD focuses on 1) an engaging, validating, curious and authentic/transparent therapist stance; 2) common factors like a) therapist relationship and repair of ruptures in the alliance; b) motivation and expectancy for change; c) emotion regulation; d) self-reflection; 3) improving team functioning by targeting potentially harmful team processes and by increasing an open and transparent discussion and collaboration; 4) institutional embedment including crisis pathways and close collaboration between different services; explicit managerial support is required as a context of peer-supervision and frequent mutual support between therapists is essential for its success. GIT-PD is manualised and has been implemented across more than 30 institutions, given its simple and straightforward approach to treatment.Format and Content of GIT-PD: GIT-PD consists of a structured pathway of episodes in treatment (assessment, middle, termination, booster) based upon a review of goals. GIT-PD assumes that, irrespective of PD type, all patients with PD share impairments in personality functioning as reflected in self and interpersonal impairments. GIT-PD is modularly designed. The structure of the GIT-PD programs includes: 1) an assessment phase including careful assessment, psycho-education, and discussion of diagnosis and case formulation; 2) a modular treatment phase, including group modules targeting core areas of PD, such as emotion regulation and interpersonal functioning; 3) additional personalised treatment modules that may include crisis planning, case management, trauma modules, family sessions and other problem-focused modules; 4) a follow-up phase with limited treatment focused at generalizing treatment benefits. Total treatment duration depends on specific patient needs but will usually vary between 12 and 18 months. GIT-PD may vary in format and content, allowing local variations to a certain extent. However, all treatments must be manualised, address specific problem areas of personality pathology, and aim at generalising treatment outcomes in daily life during the follow-up phase in order to prevent relapse and optimise participation in society again.Team discipline mix: GIT-PD is psychotherapeutically-informed. In daily practice, treatment is supervised by licensed psychotherapists, healthcare psychologists, clinical psychologists or psychiatrists and mainly delivered by other disciplines, like psychiatric nurses, social workers and Master’s level psychologists. Training is accessible to a broad range of disciplines, too.Required level of training and supervision of individual therapists: GIT-PD requires a two-day team training. Team supervision within teams will be organised according to the GIT-PD guidelines.Dosage and duration of treatment: GIT-PD has a flexible approach, enabling tailoring treatment to the clinical needs of different types of patients. The treatment duration (start-end) is 12- 18 months on average.

Thus, the generalist treatment condition reflects conditions of implementation that are easier to apply in terms of required level of training, speciality, and team discipline mix, and, additionally, it reflects a more affordable treatment format in terms of content and dosage/duration.

In comparison, the specialist treatment condition reflects conditions of implementation that are required by evidence-based specialist psychotherapy, reflecting managerial conditions, required levels of training and supervision and treatment programs that resemble the investigated evidence-based programs that are recommended by guidelines.

##### Specialist condition (MBT/ST)

For the present study, we will include currently running treatment programs of MBT and ST, given their availability within the participating institutions and strong evidence base. Specialist programs must meet the following characteristics to be eligible as part of the ‘specialist, evidence-based psychotherapy’ condition:6.Level of speciality: MBT and ST are fully manualised programs, based upon a specific theory of aetiology and pathogenesis, and both include a specific theoretical jargon and range of interventions. Both have been supported by several randomised trials and are included in all guidelines. MBT is rooted in psychodynamic and attachment theory and aims to alter personality pathology by improving mentalizing [55]. ST is an integrative treatment method, originally rooted in cognitive theory, but with additional influences from Gestalt, psychodynamic, and experiential methods [56].7.Format and Content of Specialist treatments: We chose to include only MBT and ST programs that meet the formats of the programs that have been empirically supported through randomised trials. MBT is delivered in outpatient programs as well as day hospital programs. ST has been investigated typically in individual and group formats.8.Team discipline mix: MBT and ST are psychotherapeutic programs. In daily practice, treatment is mainly delivered by licensed psychotherapists, healthcare psychologists, clinical psychologists and psychiatrists, although other disciplines could be part of the multidisciplinary team.9.Required level of training and supervision of individual therapists: The licensed psychotherapists, health care psychologists, clinical psychologists and psychiatrists in the specialist programs are required to be trained in the respective therapeutic method and registered as at least, basic-level MBT therapist or junior schema therapist or in the process of acquiring this certification through supervision by an acknowledged supervisor. The basic-level MBT certification requires a 3-day training, completing between two to four MBT treatments with people with PD, and following at least 16 supervision sessions with a licensed MBT supervisor. A junior ST therapist must complete 25 hours of ST courses, 1 year of work experience with ST, at least four ST treatments consisting of at least 100 ST sessions in total, and receive at least 20 hours of supervision by a licensed ST supervisor during these treatments. On top of that, each team should include at least one certified advanced-level specialist therapist or someone in the process of obtaining certification, referring to the MBT practitioner or senior schema therapist status. To obtain MBT practitioner status, it is required that the therapist has followed the 2-day practitioner certificate training, delivered two individual and one group MBT treatment, received 20 hours of supervision by a licensed supervisor, and attained satisfactory assessment of competencies by an independent licensed supervisor. The senior schema therapist should have completed a 25-hour advanced training, 3 years of working experience, eight ST treatments, 200 ST sessions and 40 supervision sessions with a licensed supervisor. Again, individual therapists differ across the treatment sites.10.Dosage and duration of treatment: The specialist treatment programs need to consist of a minimum of 40 sessions or a duration of 12 months, which is in line with dosage and duration of treatments evaluated in prior RCTs focusing on a population comparable to severe PD, e.g. BPD [12]. No restriction beforehand will be made on session frequency. If more than one specialist treatment (MBT or ST) or program format (e.g. intensive outpatient or day hospital MBT) is available at a site, final treatment assignment will follow the standard shared decision-making process at that site.

#### Criteria for discontinuing or modifying allocated interventions {15b}

The sponsor will suspend the study if there is sufficient ground that continuation of the study will jeopardise participant health or safety. Suspension is deemed unlikely as this study only includes regular treatment programs that have already been implemented and sustained at these sites in the Dutch mental health care system. Therapeutic progress is evaluated throughout the allocated treatment. If the therapist deems it necessary to modify the treatment, push the participant out of the allocated treatment or cross the participant over to the alternative treatment arm, then this decision needs to be discussed with the therapist in the Trial Steering Committee. Furthermore, participants can decide to discontinue the allocated treatment if desired.

#### Strategies to improve adherence to interventions {15c}

Adherence to the previously defined conditions will be measured for each site using the following criteria. For the generalist condition, the program must: a) be developed using the GIT-PD manual, b) include modules that address problem areas specific to PD, not prescribing or excluding specific techniques from other therapeutic ideologies. Instead, the GIT-PD framework implicitly and explicitly encourages therapists to use interventions that allow them to remain true to themselves by simplifying the treatment through a focus on basic principles. Furthermore, c) the integration of complete treatment programs that have a specific aetiology of PDs and are empirically supported for PDs by previous randomised studies, like MBT, ST, TFP and DBT, are excluded from the generalist condition. Additionally, the format of the generalist program should not exceed the specialist program on the same research site in terms of projected and actual treatment duration in months and dosage in minutes of treatment (per week). The projected program duration of the generalist intervention can ultimately not surpass 18 months. All the while, generalist therapists should have followed the basic GIT-PD training (2 days). Similarly, programs in the comparator/specialist condition must be designed using the treatment manual of an empirically supported MBT or ST format, including the estimated dosage and duration of the program. In addition, specialist therapists should hold a basic- or junior-level registration in their respective specialist format (MBT/ST) or be in the process of acquiring one, while at least one team member should be a fully qualified and registered MBT or advanced ST therapist, depending on the program.

For each program/team participating in the study, the following information will be collected on the organisational level: team size in staff and full-time equivalent (FTE), team composition in terms of discipline, academic level, years of experience in working with PD and MBT/ST/GIT-PD, and therapy registrations, including those for MBT and ST. For each participant, the actual duration of treatment in days, minutes of treatment, and the number of therapy sessions are obtained from the electronic patient file upon treatment completion or dropout. Furthermore, to assess the general type of institutional context and support, we will use the program adherence scale of MBT as a blueprint for identifying optimal institutional conditions for *both* specialist treatments [57], as there is no ST-specific counterpart. Additionally, we will use the quality criteria for GIT-PD from the Dutch Centre of Expertise on Personality Disorders.

#### Relevant concomitant care permitted or prohibited during the trial {15d}

Co-interventions are not offered as part of the study. Participants are, however, not explicitly prohibited from seeking additional care if desired. However, Dutch healthcare insurances cover only one PD treatment at a time. Participants are prohibited from receiving the interventions of the condition that was not allocated during randomisation for the duration of the trial.

### Outcomes {16}

The first primary outcome is the mean difference in change from baseline to end of treatment (T4) in clinician-rated personality functioning between the generalist (GIT-PD) and specialist treatment (MBT/ST) conditions, as assessed with the clinical STiP-5.1 interview. Furthermore, the second primary outcome refers to the mean difference in change from baseline to end of treatment (T4) in self-reported personality functioning between the generalist (GIT-PD) and specialist treatment (MBT/ST) conditions, based on the Level of Personality Functioning Scale – Brief Form 2.0 (LPFS-BF 2.0) questionnaire. Inclusion of the STiP-5.1 interview measure allows for blinded, clinician-rated outcome assessment, which reduces potential bias [58]. Moreover, interview measures capture a larger proportion of the variance of a latent general PD severity than self-reported questionnaires [59]. However, the use of the STiP-5.1 in psychotherapy research is novel, leading to little knowledge on the measure’s sensitivity to change [53]. Concurrently, the self-reported LPFS-BF 2.0 questionnaire has demonstrated high sensitivity to change, while its use is more established in international research [60, 61]. Therefore, the STiP-5.1 interview is given priority regarding the primary outcome, but supplemented with the self-reported LPFS-BF 2.0 questionnaire.

The secondary outcomes, among others, include the mean differences in change from baseline to the end of treatment (T4) in symptom severity (SIPP-SF, SCID-5-PQ, BSI, C-SSRS; for an outline of the here-abbreviated outcome measures, see *Plans for assessment and collection of trial data {25a})* and psychosocial functioning (WHODAS 2.0, EQ-5D-5 L, Q-LES-Q-SF) between the generalist (GIT-PD) and specialist treatment (MBT/ST) conditions. Additional secondary outcomes assess the mean differences in change from baseline to follow-up (T6) between the generalist (GIT-PD) and specialist treatment (MBT/ST) conditions in personality functioning (STiP-5.1, LPFS-BF 2.0), symptom severity (SIPP-SF, SCID-5-PQ, BSI, C-SSRS), and psychosocial functioning (WHODAS 2.0, EQ-5D-5 L, Q-LES-Q-SF). For both the short- and long-term outcomes, all available measurement points are included in the model. The secondary outcome surrounding cost-effectiveness and cost-utility of generalist (GIT-PD) versus specialist treatment (MBT/ST) addresses the incremental effects set off against the incremental costs from baseline to end of treatment (T4), calculating an incremental cost-effectiveness ratio (ICER). For the cost-effectiveness analysis, improvement in personality functioning (STiP-5.1, LPFS-BF 2.0) is set off against the incremental costs, referring to direct and indirect costs, such as treatment costs (electronic patient file data), further healthcare consumption and productivity loss (TiC-P). All the while, cost-utility is measured in quality-adjusted life years (QALYs) gained throughout the assigned intervention, calculated from EQ-5D-5L scores. The final secondary outcome measures the combined predictive value of end-of-treatment differential treatment response, based on several pre-randomisation variables. The predictive value is expressed in a personal advantage score in terms of LPF improvement from baseline (STiP-5.1, LPFS-BF 2.0). The pre-randomisation variables with prescriptive and/or prognostic value are selected and used for predicting advantage scores through the development of a PAI algorithm. For a detailed description of the instruments and the timeline of assessment, see *Plans for assessment and collection of outcomes {25a}* and *Participant timeline {18}*.

### Harms {17}

As participants follow regular treatments offered within the Dutch mental healthcare system, no increased risk of harm surrounding participation is anticipated. Unanticipated adverse events (AE) and serious adverse events (SAE) are, however, addressed in multiple ways. AEs are defined as any undesirable experience occurring to a participant during the study, regardless of whether it is considered related to the experimental or comparator interventions. An SAE is defined as any untoward medical occurrence or effect that: a) results in death; b) is life threatening (at the time of the event); c) requires hospitalisation or prolongation of existing inpatients’ hospitalisation; d) results in persistent or significant disability or incapacity; e) is a congenital anomaly or birth defect; or f) any other important medical event that did not result in any of the outcomes listed above due to medical or surgical intervention but could have been, based upon appropriate judgement by the investigator. SAEs and spontaneously reported AEs by the participant will be reported to the PI within 24 hours by the corresponding participating institution. All AEs and SAEs are recorded by the PI. SAEs must be reported to the accredited medical ethical research commission (METC Brabant) in a yearly listing.

To further increase participant safety, results on the suicidality screener (see *Columbia – Suicide Severity Rating Scale Screener/Recent Self-report (C-SSRS)*) are routinely monitored by the junior researchers. In case of a participant reporting heightened levels of suicidality, the participant’s principal therapist will be informed to prevent an SAE.

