#### Plans to Promote Participant Retention and Complete Follow-Up {25b}

Participant retention is promoted through multiple strategies aimed at a personalised approach that minimises burdens and maximises accessibility [114, 115]. Whenever possible, existing data is reused to avoid redundant assessments. For example, STiP-5.1 interviews conducted during regular intake are repurposed for eligibility assessment and baseline measurements. Routine outcome monitoring (ROM) is adapted to prevent overlap with study instruments and again supplemented with SIPP-SF and BSI results at designated time points to facilitate usage during treatment trajectories. Before each assessment, research staff call participants to discuss their availability and preferred mode of completion (online or in-person), ensuring a participant-centred approach. Online assessment is set as the default to enhance convenience. Furthermore, participants receive a total reimbursement of €50, distributed across T1 (€15), T4 (€20), and T6 (€15). If a participant considers dropping out, research staff will encourage continued participation by offering a reduced test battery focused on collecting the primary outcomes at T4 and T6. The extent of this set depends on the participant’s willingness.

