
To answer the secondary research questions regarding long-term (T6; 30 months) non-inferiority of generalist (GIT-PD) versus specialist treatment (MBT/ST) in improving personality functioning, an identical intention-to-treat longitudinal multilevel model will be fit as for the primary outcome, while including all available repeated measures. This ultimately results in the inclusion of three and seven repeated measures for the STiP-5.1 and LPFS-BF 2.0, respectively. Likewise, to assess the short-term (T4; 18 months), as well as the long-term (T6; 30 months) non-inferiority of generalist (GIT-PD) versus specialist treatment (MBT/ST) in improving symptom severity and psychosocial functioning, the same intention-to-treat longitudinal multilevel model will be applied for each of the secondary study parameters (SIPP-SF, SCID-5-PQ, BSI, C-SSRS, WHODAS 2.0, EQ-5D-5 L, Q-LES-Q-SF). Likewise, for the short-term outcome, the five repeated measures (level 1) of each individual (level 2) are nested within treatment sites (level 3). Models are adjusted for the respective outcome’s baseline value, random intercepts, and slopes are modelled at the second and third level to account for heterogeneous individual and treatment site change trajectories over time, and two-tailed significance levels are set at *α* = 0.05, while effect estimates are reported with corresponding 95% two-sided confidence intervals. The non-inferiority margin is set at *d* = − 0.25. On top of that, all AEs and SAEs are descriptively reported for both treatment arms.

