Another potential concern is the difference in average treatment duration between conditions. Indeed, treatment dosage and duration are among the defining distinctions between the generalist and specialist approaches. In line with previous trials, specialist treatments are expected to be delivered at a significantly higher dosage than the generalist condition. To ensure comparability between conditions, assessment time points are scheduled at fixed intervals, independent of treatment type. The primary endpoint is set at 18 months after treatment initiation, aligning with the projected average treatment duration for specialist treatments. While actual treatment durations may vary at the individual level, the intensive treatment phase is expected to be completed in all programs by this 18-month mark, with only low-intensity booster sessions continuing beyond this point. Therefore, the 24-month time point has been designated as the post-booster follow-up, by which time treatment trajectories in both conditions will have concluded for nearly all participants. This alignment of measurement time points ensures comparability in evaluating (cost-)effectiveness across conditions. Furthermore, the extended follow-up assessments at 24 and 30 months allow for the examination of potential delayed or sustained effects related to differences in treatment duration.

In conclusion, P-DAET will be the first randomised controlled trial to compare the non-inferiority of a generalist treatment approach (GIT-PD) directly to specialist treatments (MBT/ST) for individuals with severe personality disorders, as defined by the AMPD. This study is expected to generate novel insights into the effectiveness and real-world applicability of both generalist and specialist interventions. It will also address which patient needs are better met by more expensive specialist interventions. In this way, it contributes to a greater accessibility for all patients with severe personality disorders as well as an empirically supported assignment of these patients to different treatment types.

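### Non-serious adverse events are taken only from spontaneous reports passed on by institutions whose contact with participants differs by arm, so the by-arm harms table may under-count generalist events

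*Protocol article*

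**What the plan says.** All references are to the protocol article.

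- **Definition.** The Harms section is broad: "AEs are defined as any undesirable experience occurring to a participant during the study", whether or not the event is thought related to treatment.
- **Route.** The same section then states: "SAEs and spontaneously reported AEs by the participant will be reported to the PI within 24 hours by the corresponding participating institution".
- **Suicidality.** Results on the C-SSRS screener "are routinely monitored by the junior researchers". If a participant reports heightened suicidality, the "principal therapist will be informed to prevent an SAE".
- **Analysis.** The statistical methods section (27a) says that "all AEs and SAEs are descriptively reported for both treatment arms". No test is planned.
- **Contact by arm.** The Discussion says that "specialist treatments are expected to be delivered at a significantly higher dosage than the generalist condition". The adherence section (15c) requires that "the format of the generalist program should not exceed the specialist program on the same research site", in duration and in weekly minutes.
- **Research contact.** Assessments run at fixed times that do not depend on the treatment. The retention section (25b) adds: "Before each assessment, research staff call participants to discuss their availability and preferred mode of completion".

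**The concern.** The definition covers every undesirable experience and the analysis promises all of them by arm, but the collection rule brings in non-serious events only when a participant mentions them unprompted. Participants in the more intensive arm have more occasions to do so. Neither participants nor therapists are blinded.

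If reporting rises with contact, the experimental arm is the one that is under-counted. The trial asks whether a less intensive treatment is good enough, and readers will look at the harms table beside the efficacy result. No data monitoring committee is planned and SAEs go to the ethics committee as a yearly listing, so that table is the main comparative account of adverse events. An apparent balance, or an apparent advantage for generalist treatment, could come from how events were noticed.

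**Working it through.** The plan states no harms figure, so there is none to reproduce. The check sets the provisions side by side and then illustrates the possible size.

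**1. What reaches the trial, by type of event**

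| Event | Stated route | Depends on treatment contact? |
|---|---|---|
| Non-serious AE | Volunteered by the participant, passed on by the institution | Yes, plausibly |
| SAE | Reported by the institution; not limited to spontaneous reports | Less so (death, admission) |
| Suicidality | C-SSRS self-report, monitored centrally in both arms | No, but logging a signal as an AE is not stated |
| Healthcare use | TiC-P, a cost questionnaire | No, but no link to AE/SAE recording is stated |

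The TiC-P recalls 3 months and is extrapolated linearly over longer intervals. From 6 months onward, assessments are 6 months apart (6, 12, 18, 24, 30), so even if given at each of them it would ask about 3/6 = half of each interval. Costs can be extrapolated in this way; individual events cannot.

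**2. Does contact differ by arm?**

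- Dosage: yes, by design (Discussion and section 15c). No number of sessions or minutes per arm is given.
- Duration: less clearly. Generalist treatment averages 12 to 18 months. Specialist programmes need at least 40 sessions or 12 months, with a projected average of 18 months. These overlap, and both arms have a follow-up or booster phase.

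The firm difference is therefore dosage.

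**3. Illustration of size (assumed inputs)**

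Observed risk = true risk × share reported. With equal true risks,

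observed ratio (generalist/specialist) = share reported, generalist ÷ share reported, specialist.

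The inverse is the true ratio that would appear as 1.00. Counts use 179 participants per arm (sample size section) and an assumed true risk of 30%. For example, specialist at 90%: 179 × 0.30 × 0.90 = 48.3; generalist at 70%: 179 × 0.30 × 0.70 = 37.6.

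| Share reported, specialist / generalist | Observed ratio if true risks are equal | Participants with an AE, specialist / generalist | True ratio that would appear as 1.00 |
|---|---|---|---|
| 100% / 100% | 1.00 | 53.7 / 53.7 | 1.00 |
| 90% / 80% | 0.80/0.90 = 0.89 | 48.3 / 43.0 | 0.90/0.80 = 1.13 |
| 90% / 70% | 0.70/0.90 = 0.78 | 48.3 / 37.6 | 0.90/0.70 = 1.29 |
| 90% / 60% | 0.60/0.90 = 0.67 | 48.3 / 32.2 | 0.90/0.60 = 1.50 |
| 80% / 40% | 0.40/0.80 = 0.50 | 43.0 / 21.5 | 0.80/0.40 = 2.00 |

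At an assumed true risk of 10%, 90% against 70% gives 16.1 and 12.5 participants. The ratio is unchanged, but the gap in counts is small.

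**The case against.** The strongest reply has five parts.

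- **The wording limits AEs, not SAEs.** This stands. A reader might infer that all harms are collected only by spontaneous report, but the sentence does not say so. Deaths and admissions depend less on session contact.
- **Arm-symmetric measures exist.** This stands in part. The C-SSRS is given in both arms and analysed as a secondary outcome, and worsening would also show on scales such as the BSI and WHODAS 2.0. The C-SSRS assesses suicidal ideation, however, and the article does not say that a signal becomes a recorded AE. None of these scales records other events.
- **Duration and follow-up contact.** A reader might infer that generalist participants go unobserved for longer after treatment. The documents do not support this: the durations overlap, booster contact is foreseen, and research staff contact both arms up to 30 months.
- **No reporting rates are given.** This stands. That the table will be biased is more than the documents show, and more treatment contact could itself cause or prevent events. The bias is a risk with a plausible direction and no known size.
- **The article is a condensed protocol.** Event forms and prompts may well be left to the full document. But the point rests on a rule that the article states, namely spontaneous reporting, and not on a missing detail. If the full protocol solicits events, the article's sentence is wrong and should be changed to match.

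**Conclusion.** The point holds in limited form. Followed as written, the plan takes non-serious AEs only from volunteered reports and routes AEs and SAEs through institutions whose contact differs by design. The by-arm AE table may therefore under-count events in the generalist arm.

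The direction rests on one assumption: that the share of events reported rises with treatment contact. The size cannot be determined from the documents. Under the assumed shares above, equal true risks would appear as ratios between 0.50 and 0.89. The exposure is smaller for SAEs and for suicidality. The primary non-inferiority analysis and the sample size are not affected. It is worth correcting because the remedy is cheap and events that were never asked about may not be recoverable later.

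**What to change.** 1. **Harms section.** Add the same short structured AE/SAE question in both arms at T1 to T6, covering the full interval since the last assessment. Place it in the existing CASTOR self-report package, or have it asked by staff confirmed as unblinded. The pre-assessment call is suitable only if its callers are unblinded, which the retention section does not state. This protects the blinding of the STiP-5.1 assessors.
2. **Harms section.** State whether C-SSRS signals and hospital admissions reported on the TiC-P are recorded as AEs or SAEs.
3. **Section 27a.** Make the solicited events the by-arm harms summary and list spontaneous reports separately.

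The cost is a protocol amendment, one short form, slightly more participant burden and a higher number of recorded events. Enrolment is planned to the end of 2026 and data collection to December 2029, so an early amendment would still reach assessments that lie ahead. The report should say from when the question was in use.
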